## Abstract

**Background:** Depression is a growing public health concern that negatively impacts work ability and performance. Psychiatric nurses have an elevated risk for depressive symptoms, and it is essential to ensure their good mental health and work ability. The association between nutrition and depression is recognized, but there is a need for randomized, controlled intervention studies investigating the effectiveness of diet on depressive symptoms and related work impairment. **Aim:** Mind Nutrition is a randomized, controlled intervention study examining whether improving nutrition can reduce depressive symptoms and depressive symptoms-related sick leaves and enhance work ability and quality of life among mental health and substance abuse professionals. **Methods:** We will recruit 125 nurses and social welfare professionals from the mental health and substance abuse field of the Satakunta Wellbeing Services County. Half of the participants will be randomized to the intervention and half to the control group. Subjects in the intervention group will participate in two individual and three group counselling sessions during a 6-month intervention. Nutrition counselling follows the Finnish Nutrition Recommendations. The control group will maintain their habitual diet. The Center for Epidemiological Studies – Depression, depressive symptoms-related sick leave days, two work ability indicators, a Food Frequency Questionnaire, three-day food records, Three-Factor Eating Questionnaire – 18 and WHO-8 Eurohis Quality of Life will be assessed at baseline and 6 months. **Summary:** This study will provide evidence of the effectiveness of nutrition counselling on depressive symptoms and related sick leave days, work ability and quality of life.

## Introduction

Depression is a common mental disorder, with around 280 million people in the world suffering from it (World Health Organization [WHO], 2023). It negatively affects the quality of life, including social life, emotional and physical well-being and work life. At the societal level, depression causes a substantial economic burden. It is associated with greater work absenteeism, short-term disability, decreased productivity and presenteeism (Brandford and Reed, 2016). The Organisation for Economic Co-operation and Development (OECD, 2018) has estimated the total costs of mental health problems in Europe to be more than EUR 600 billion yearly which is more than 4% of the gross domestic product.

Treating depressive symptoms at an early stage is crucial for preventing their aggravation (Kessler et al., 2003). Nurses have a two-fold risk of depression compared to those in other professions (Brandford and Reed, 2016), with mental health nurses experiencing particularly high levels of depressive symptoms (Brandford and Reed, 2016; Opoku Agyemang et al., 2022; Tsaras et al., 2018). Recommendations for prevention include lifestyle interventions, focusing on exercise, healthy diet, social relationships and adequate and good quality sleep (Finnish Current Care Guidelines for Depression, 2024; World Health Organization, 2023). There is convincing evidence for the link between the Mediterranean diet (Serra-Majem et al., 2020) and a lower dietary inflammatory index and a lower risk of depression (Gianfredi et al., 2023). The relationship between diet and depression is likely bidirectional. The biological mechanisms linking nutrition to depression include, for example, gut microbiota, low-grade inflammation, epigenetic changes and oxidative stress (Marx et al., 2021).

Mediterranean diet interventions, utilizing either individual or group counselling, have significantly improved moderate to severe depressive symptoms (Bayes et al., 2022; Francis et al., 2019; Jacka et al., 2017; Parletta et al., 2019), with two studies demonstrating good results in cost-effectiveness analyses (Chatterton et al., 2018; Segal et al. 2020). The studies have reported a reduction in depression to mild or sub-clinical levels (Bayes et al., 2022; Francis et al., 2019; Jacka et al., 2017; Parletta et al., 2019) and an association between improved diet and reduced depression (Francis et al., 2019; Jacka et al. 2017; Parletta et al., 2019). Other intervention studies are predominantly based on secondary analyses and are heterogeneous regarding depression definition and methods (Firth et al., 2019; O’Neill et al., 2022). The MooDFOOD depression prevention study (Bot et al., 2019) using nutrition-focused behavioural therapy, multi-nutrient supplement or a combination found positive effects only among active participants and those with high baseline depressive symptoms.

To our knowledge, the effects of nutrition on depression-related work disability have not been researched before. One study found associations between dietary factors and burnout symptoms, indicating that nutrition does have a role in coping at work (Penttinen et al., 2021). Overall, lifestyle interventions have shown their potential to improve the work ability and productivity of the workforces (Grimani et al., 2019). People with a high depression risk should be a key target group for interventions to reduce work disability (Wedegaertner et al., 2013). Nutrition interventions could reduce the economic burden of depression by also preventing physical comorbidities of depression, such as obesity (Luppino et al., 2010), type 2 diabetes (Semenkovich et al., 2015) and cardiovascular diseases (Krittanawong et al., 2023).

The primary aim of the Mind Nutrition randomized controlled trial is to examine the effectiveness of nutrition counselling on depressive symptoms and work ability among nurses and social services professionals working in the mental health and substance abuse fields. The secondary aims are to examine the effectiveness of depression-related sick leave days, quality of life and dietary habits. This article is a detailed description of the study protocol. This is the first study that provides evidence on the effects of nutritional counselling on depressive symptoms, work absenteeism and work ability among mental health professionals.

## Methods

### Participants and recruiting

#### Participants

We will recruit 125 licensed practical nurses, registered nurses, mental health nurses and social services professionals in the mental health and substance abuse fields in Pori, Satakunta Wellbeing Services County, Western Finland. We will recruit participants working in special care and primary care, outpatient departments, institutional care and rehabilitation services. The inclusion and exclusion criteria are as follows:

*Inclusion criteria:*
1.Aged 18 years or over2.Adequate Finnish language skills3.Work-capable4.Currently employed by Satakunta Wellbeing Services County for at least 6 months5.Works in the mental health and substance abuse fields6.Education is in one of the following areas: licensed practical nurse, registered nurse, mental health nurse or has a bachelor's degree in social services7.Agrees to commit to either of the groups (intervention/control) during the 6 months of intervention8.Able to give informed consent.

*Exclusion criteria:*
1.Acute mental health symptoms and inability to work2.Terminal phase disease or unstable severe chronic disease (consultation with the responsible physician)3.Employed for a shorter period than 6 months4.History of eating disorder (consultation with the responsible physician)5.A score of ≥16 on the CES-D (Center for Epidemiological Studies – Depression) scale (Radloff, 1977) and reduced work capacity (determined in consultation with the medical expert in mental health)6.Substance abuse based on the Alcohol Use Disorder Identification Test – Consumption (AUDIT-C) score (consultation with the responsible physician)

#### Sample size calculation

We calculated the sample size based on the expected change in depressive symptoms, measured with the CES-D scale (Radloff, 1977). We expect depressive symptoms to decrease in the intervention group from 14 to 9.9 points (Katsuta et al., 2021; Konttinen et al., 2010; Mondal et al., 2022) and assume that depressive symptoms will not change in the control group. The calculation is based on an estimated power of 0.8 with an expected dropout rate of 25%. The calculated sample size was 125, meaning 62 or 63 participants per group (ß = 0.2, a 0.05).

#### Recruitment

We will organize an informational online meeting for targeted participants in which we will explain the study procedure (Figure 1). Interested participants can register for the second informational meeting, consisting of a detailed description of the study, the inclusion and exclusion criteria and the instructions for filling in the questionnaires and food records. The principal researcher will evaluate the eligibility of the interested participants who can give informed consent at the end of the second meeting. Subsequently, we will schedule individual appointments with a research nurse and ask the participants to fill in the questionnaires before the appointments. The research nurse will measure blood pressure and weight, check the questionnaires and confirm whether the subject is eligible to participate. If the questionnaires reveal something that falls under the exclusion criteria, the research nurse can consult with the responsible physician. Exclusion of the participant is possible at this point.

**Figure 1. fig1-02601060251332358:**
[figure not shown]
Flow chart of the study.

### Randomization

After baseline measurements and confirming that they meet the inclusion criteria, the participants will be randomly allocated in a 1:1 ratio into the intervention or control groups according to a computer-generated, blocked randomization list. A person unrelated to the study will conduct the randomization. For the participants in the intervention groups, the 6-month nutrition intervention period starts on the first day of nutritional counselling, whereas for the participants in the control group, it starts on the day randomization will be conducted. The control group will not receive any intervention but will continue their habitual diet. We will offer the control group one nutrition counselling session after the end of the intervention.

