#### Primary and secondary outcomes

Table 1 presents the primary and secondary outcomes. The outcomes will be assessed utilizing the electronic survey at baseline and after 6 months.

**Table 1. table1-02601060251332358:** Primary and secondary outcomes.

Primary outcome variables	Measurement
Depressive symptoms	CES-D (Radloff, 1977)
Work ability	Current work ability compared with the lifetime best (Tuomi et al., 2007) Three-level work ability indicator (Gould et al., 2015)
Secondary outcome variables	Measurement
Sick leave days related to depressive symptoms	Structured question about sick leave days during the past 6 months
Quality of life	WHO8-EUROHIS (WHO, Power, 2003)
Dietary habits	Food Frequency Questionnaire (Männistö et al., 1996) Healthy Diet Index (HDI; Lindström et al., 2021) Three-day food records Three Factor Eating Questionnaire – 18 (TFEQ-18; Karlsson et al., 2000)
Intervention adherence	Goal Attainment Scaling (GAS; Kiresuk and Sherman, 1968) Level of participation
Intervention acceptability	The Theoretical Framework for Acceptability (TFA; Sekhon et al., 2022)

CES-D: Center for Epidemiological Studies – Depression; TFEQ-18: Three Factor Eating Questionnaire – 18; WHO: World Health Organization.

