##### Secondary outcome: Change in sick leave days related to depressive symptoms

We will measure depression-related sick leave days during the past 6 months. The question has the following response options: No days, 0–6 days, 7–14 days, 15–29 days, 30–49 days and 50 or more days.

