#### Individual counselling

The main contribution of the intervention is the individually tailored nutrition counselling provided to each participant by the same research nutritionist. The focus is on the personal goal towards the adoption of the recommended diet by participants through personalized goal setting. The first individual counselling session lasts 1–1.5 h. During the first session (Table 3), the nutritionist evaluates the participant's background factors, dietary habits, nutrient intake and eating behaviour. The participant sets adequate goals and means to achieve them with the nutritionist. The framework is the GAS method (Kiresuk and Sherman, 1968). Goals and means will be written in the personal nutrition plan. During the second individual meeting (1 h), the achievement of the goals will be assessed using the GAS method (Kiresuk and Sherman, 1968) and potential challenges and solutions will be discussed by applying the principles of motivational interviewing (Miller, 1996).

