### Statistical analyses

The results will be analysed using the IBM SPSS Statistics program and the STATA program. A statistician unrelated to the study will perform the statistical analyses. The analyses will utilize the intention-to-treat principle (Soares and Carneiro, 2002).

The normality of variables will be examined graphically and using the Shapiro–Wilk test. For the descriptive statistics, comparisons between groups will be analysed using the independent samples *t*-test for continuous, normally distributed variables, the chi-squared test for categorical variables and the Mann–Whitney *U* test for non-normally distributed variables. The difference between groups in the change in depressive symptoms, quality of life and diet quality is continuous variables and will be analysed with repeated analysis of variance. The difference between groups in the change in work ability and sick leave days related to depressive symptoms is ordinal variables and will be analysed with mixed-effect models for ordinal data. The main outcomes will be examined first overall and then stratified by gender to assess potential gender differences in intervention effectiveness.

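### The 6-month period starts at first counselling in one arm and at randomisation in the other, and no other anchor is given for the final outcome assessment

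*Protocol article*

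**What the plan says.** All references are to the protocol article.

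- **Order of events** (Randomization): "After baseline measurements and confirming that they meet the inclusion criteria, the participants will be randomly allocated in a 1:1 ratio". Baseline therefore comes before allocation in both arms.
- **Start of the period** (Randomization): for the intervention arm, "the 6-month nutrition intervention period starts on the first day of nutritional counselling"; the same sentence continues, "whereas for the participants in the control group, it starts on the day randomization will be conducted".
- **Outcome timing** (Primary and secondary outcomes): "The outcomes will be assessed utilizing the electronic survey at baseline and after 6 months". Table 2 likewise places the final measurements at 6 months. Neither names the date from which the 6 months run.
- **Sick leave** (the secondary outcome section on sick leave days): "We will measure depression-related sick leave days during the past 6 months".
- **Analysis** (Statistical analyses): "The analyses will utilize the intention-to-treat principle". The change in depressive symptoms "will be analysed with repeated analysis of variance", with no term described for elapsed time.
- **Delivery** (Individual counselling): "individually tailored nutrition counselling provided to each participant by the same research nutritionist", with a first session of 1–1.5 h. Table 3 lists this individual session first.

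The article does not limit the time from randomisation to first counselling, and gives no start date for an allocated participant who does not attend.

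**The concern.** This is a rule the article states, and states differently by arm, so it cannot be put down to detail left to a fuller document. If the final survey follows that rule, three things depend on arm.

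1. **Elapsed and calendar time.** The interval from baseline to the final CES-D is longer in the intervention arm. CES-D asks about the past week, so its date matters whenever mood varies with season, workload or time since enrolment.
2. **Sick-leave coverage.** The final 6-month recall looks back to randomisation in controls but only to the first session in the intervention arm.
3. **Participants who never start.** If the start date is individual, a person allocated to counselling who never attends has no time zero and hence no due date for the final survey. Only the intervention arm can have such people.

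The first point touches a primary outcome. Assessment dates cannot be realigned once the data have been collected.

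**Working it through.** **Plan's own figures.** The article gives no figure for the delay, so there is none to reproduce. The sample size of 125 plays no part in this point. The planned CES-D effect, 14 − 9.9 = 4.1 points with no change in controls (Sample size calculation), serves only as a yardstick.

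**Step 1: timeline.** Let B be the baseline survey, R randomisation and S the first session, with g = R − B and d = S − R. Assume that the final survey follows the clock in the Randomization section.

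| | Control | Intervention |
|---|---|---|
| Final survey | R + 6 months | S + 6 months |
| Baseline-to-final interval | g + 6 months | g + d + 6 months |
| Final sick-leave window | R to R + 6 months | S to S + 6 months |
| Time after B in neither recall window | g | g + d |

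Both arms have the gap g. Only the extra d differs by arm. The recall window is 6 months long in both.

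**Step 2: size of d.** Inputs are 62–63 participants per group (Sample size calculation) and first sessions of 1–1.5 h (Individual counselling). Contact time is 62 × 1.0 = 62 h to 63 × 1.5 = 94.5 h. Sessions per day are not stated; 2–4 is an assumption, as are one nutritionist for everyone and a 5-day week. With a steady queue, the mean delay is half the last delay.

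- *All randomised together (assumed):* 62.5 / 4 = 15.6 working days = 3.1 weeks; 62.5 / 2 = 31.25 working days = 6.25 weeks. The last start is about 3–6 weeks after randomisation, with a mean delay of about 1.6–3.1 weeks.
- *Waves of 15–20 (assumed, matching the counselling group size under Intervention):* 15 / 4 = 3.75 working days = 0.75 weeks; 20 / 2 = 10 working days = 2 weeks. The last start is about 1–2 weeks after randomisation, with a mean delay of about 0.4–1 week.

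Against 26 weeks in controls, the mean time from randomisation to final survey in the intervention arm would be 27.6–29.1 weeks in the first case and 26.4–27.0 weeks in the second.

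**Step 3: effect on the CES-D contrast.** Shift = drift per month × mean delay in weeks / 4.345. Drift means change that would occur regardless of treatment. The rates below are assumptions.

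| Mean delay (weeks) | Drift 0 | 0.25/month | 0.5/month | 1/month |
|---|---|---|---|---|
| 0.4 | 0 | 0.02 | 0.05 | 0.09 |
| 1.0 | 0 | 0.06 | 0.12 | 0.23 |
| 1.6 | 0 | 0.09 | 0.18 | 0.37 |
| 3.1 | 0 | 0.18 | 0.36 | 0.71 |

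For example, 0.5 × 3.1 / 4.345 = 0.36 points, and 0.36 / 4.1 = 9% of the planned effect. The largest entry is 0.71 / 4.1 = 17%; with no drift the shift is nil. The sign follows the direction of drift, which is unknown.

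**Step 4: never-starters.** S is undefined for them on a per-participant reading, so S + 6 months is undefined too. With R as time zero, R + 6 months exists for everyone randomised, and the planned difference in assessment time between arms is 0.

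**The case against.** The strongest reply is that the Randomization section defines when the intervention period starts, and does not say when the final survey is sent. A reader might infer as fact that the arms are measured at systematically different times. The article does not state that; it is the natural inference, because no other 6-month anchor appears. The flow chart in Figure 1 was not available in the text reviewed. This part of the reply stands as a limit on certainty. It does not remove the need to reconcile the sections.

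Other stronger readings also fail:

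- **A delay of several weeks is not established.** The 3–6 week figure needs everyone randomised together and served from one queue. Baseline visits are booked individually, and counselling groups hold 15–20, so entry in waves is plausible and the delay then much shorter. The wording on the same nutritionist could also mean continuity for each participant and not one provider for all.
- **Controls do not have complete sick-leave coverage.** They too have an uncovered stretch, from baseline survey to randomisation. Recall length is equal in both arms, and the answers are wide bands.
- **It does not follow that randomisation ceases to protect the comparison.** CES-D bias needs drift independent of treatment, and the sample size section assumes no change in controls.
- **There is no outright contradiction with intention-to-treat.** That principle concerns analysis as allocated; an undefined survey date is a scheduling gap. It would disappear if the first counselling day were a common date for the group, which the text neither says nor rules out.

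**Conclusion.** The concern holds in limited form. The article gives one 6-month period two different starts by arm and offers no other anchor for the final outcomes. Followed as written, it makes assessment timing depend on arm, adds an uncovered sick-leave stretch equal to the counselling delay in the intervention arm only, and, on a per-participant reading, leaves never-starters without a due date.

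The size is unknown because the delay is not stated. Under the assumptions shown, the mean delay is somewhere between 0.4 and 3.1 weeks, and the CES-D shift runs from nil without drift to 0.71 points at an assumed 1 point per month. Its direction cannot be given. The sick-leave mismatch needs only a delay and no drift. The documents do not support a claim that the trial's result will be biased. They do support correcting the rule before final assessments are scheduled.

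**What to change.** Define time zero for outcome assessment as the randomisation date in both arms. Send the final survey and book the final nurse visit 6 months after randomisation, within one common stated window, for everyone randomised, whether or not and whenever counselling began. Alternatively, randomise in batches and set one common final-assessment date per batch for both arms. Report the delay from randomisation to first session descriptively. If the sponsor already intends a common anchor, a sentence saying so in the outcomes section, with the Randomization section brought into line, is enough.

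The cost is wording and scheduling; the sample size of 125 does not change. The downside is that late starters have slightly less counselling time before the final assessment. It should be small: the Intervention section has five sessions held monthly, which span about four months from first to last (four intervals), so a start a few weeks after randomisation would still leave room for all five before a 6-month assessment.

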### Measurements

#### Background measurements

Background information will be collected before the randomization, utilizing the electronic survey data, and the weight and blood pressure measured at the research nurse appointments. The electronic survey will have questions about family relations, education, basic employment information and lifestyle habits, including the AUDIT-C (Saunders et al., 1993). The research nurse appointments will be organized at the university. The nurse will check the electronic questionnaire, blood pressure and weight during these appointments. We will calculate body mass index based on the measured weight and participants’ self-reported height. Although the primary focus of our intervention is not on body weight loss, we will measure it to consider the possible effect that weight loss could have on depression scores (Patsalos et al., 2021).

